## 5. Materials and Methods

### 5.1. Study Design

This cohort study is designed as a natural experiment and includes seven level 2 trauma centers across The Netherlands. Participating hospitals follow either an expert-based protocol permitting surgery within 24 h after the last DOAC intake or a conservative protocol requiring a minimum delay of 24 h. Patient inclusion starts in November 2025 and is expected to conclude in June 2027.

### 5.2. Natural Experiment

#### 5.2.1. Rationale

Natural experiments are observational studies in which treatment allocation is determined by external factors rather than by investigators, closely resembling the principles of randomization [42]. In the context of orthopedic trauma, natural experiments remain relatively uncommon, but offer significant potential due to existing variability in treatment strategies between hospitals or regions [42]. These differences often stem from local education, institutional culture, and expert opinion [42]. By leveraging these naturally occurring variations, this study aims to evaluate treatment outcomes without altering clinical practice.

This study follows the principles outlined by the Natural Experiments (NEXT) Study Group, which provides methodological guidance for designing natural experiments in trauma research [42]. Key design features include the use of distinct “schools of treatment” where institutional protocols consistently determine care, while patient allocation to hospitals occurs independently of individual characteristics [42]. To support comparability between groups, all participating hospitals are level 2 trauma centers with similar hip fracture volumes, staffing, and standardized perioperative care. These similarities reduce the chance that outcome differences are due to institutional differences.

Importantly, this study constitutes a Type 2 Comparison in orthopedic trauma surgery, as defined by Beks et al., in which two active treatment strategies (early versus delayed surgery) are compared for the same clinical indication [43]. Observational studies are particularly well suited for this type of comparison when treatment allocation is determined by institutional protocols or surgeon preference rather than individual patient characteristics [43,44]. This scenario is common in trauma care, where patients are often assigned to hospitals or surgical teams based on logistical factors, resulting in quasi-randomization in treatment [42,43]. This quasi-randomization reduces the effect of confounding and selection bias and strengthens the validity of the comparisons [42,43]. Nevertheless, as with all observational designs, the possibility of residual unmeasured confounding cannot be entirely excluded [43,44,45].

Despite this, well-designed observational studies, particularly natural experiments, can yield results similar in credibility to randomized controlled trials (RCTs) [43,44]. In addition, RCTs are often impractical or unethical in trauma research due to the urgency of treatment decisions, challenges in obtaining informed consent in acutely injured or cognitively impaired patients, and the logistical difficulties of randomization in acute care settings [42,43]. Natural experiments thus represent a methodologically sound and ethically viable alternative for evaluating treatment effectiveness in real-world trauma care [42,43].

#### 5.2.2. Treatment Allocation

Participating hospitals are divided into two cohorts based on the pre-existing “schools of treatment”, reflecting distinct institutional protocols and inherent differences in the clinical management of hip fracture patients on DOACs [42]. School “A” (early surgery cohort) comprises three hospitals and School “B” (delayed surgery cohort) four hospitals, ensuring broad geographic distribution across The Netherlands (Appendix A; Figure A1). In the hospitals belonging to School “A”, the standing policy is to perform surgery on hip fracture patients on DOACs within 24 h after last DOAC intake. In contrast, hospitals in School “B” follow a strict protocol requiring a delay of at least 24 h after last DOAC intake before surgery to allow for DOAC clearance. One participating hospital applies a mixed protocol: delaying prosthesis surgery for 24 h after the last DOAC intake while performing all other procedures within 24 h. This setting still constitutes a natural experiment because allocation to early or delayed surgery is determined solely by the local institutional protocol rather than by surgeon, patient, or researcher intervention. In rare cases where deviation from the protocol occurs, for example, due to medical urgency in School “B” or logistical or clinical reasons in School “A”, these patients will be identified and handled accordingly in the analyses. The analytic plan for handling these deviations is further described in Section 5.8.

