#### 5.2.3. Policy Changes

Initially, allocation to these groups occurs naturally based on the hospital where the patient is admitted, rather than by investigator intervention, ensuring that treatment allocation is independent of individual patient characteristics. However, in the unlikely event that during the study (orthopedic) trauma surgeons within School “B” change their protocol and start performing surgery within 24 h after last DOAC intake, these patients will be included in School “A”. Conversely, if surgeons within School “A” change their protocol to delay surgery at least 24 h after last DOAC intake, patients from that point onward will be included in School “B”. In both cases, allocation will then be based on surgeon-level protocol rather than hospital-level standard practice. Despite this, the study remains a natural experiment, as patients continue to be quasi-randomly allocated to comparable level 2 trauma centers with uniform hospital resources and patient populations.

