**Figure 2 jcm-15-00758-f002:**
[figure not shown]
Flowchart of cohort allocation and analysis plan. Patients are quasi-randomly assigned to cohorts based on hospital protocol. Per-protocol analysis includes only patients treated according to their hospital’s policy. * An intention-to-treat analysis will be performed to assess robustness and preserve quasi-randomization, meaning that patients are analyzed according to their initially assigned cohort based on hospital protocol, irrespective of protocol deviations.

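### One of the seven hospitals sets timing by procedure, which confounds procedure with timing in the unadjusted primary risk difference; and the surgeon-level reallocation rule conflicts with the hospital-based per-protocol and ITT definitions.

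*Protocol article*

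**What the plan says.** Section 5.2.2 divides the seven hospitals into School A (three, early surgery) and School B (four, delayed surgery). It then says "One participating hospital applies a mixed protocol", namely "delaying prosthesis surgery for 24 h after the last DOAC intake while performing all other procedures within 24 h". It maintains that allocation is still "determined solely by the local institutional protocol rather than by surgeon, patient, or researcher intervention".

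Section 5.2.3 describes allocation by admitting hospital as "ensuring that treatment allocation is independent of individual patient characteristics". It then provides for a change of practice, which it regards as unlikely. Patients of School B surgeons who start operating early are counted in School A, and the reverse applies to School A surgeons who start delaying. It adds: "In both cases, allocation will then be based on surgeon-level protocol rather than hospital-level standard practice".

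Section 5.8.1 judges per-protocol adherence against the timing protocol of the patient's hospital, excludes deviating patients, and defines ITT by the admitting hospital's timing policy. The Figure 2 legend says that in the ITT analysis "patients are analyzed according to their initially assigned cohort based on hospital protocol, irrespective of protocol deviations". The non-inferiority decision rests on a risk difference with a one-sided 95% confidence limit, described without adjustment. Procedure type is among the variables considered for an additional logistic model that yields an adjusted odds ratio. Propensity score matching is a sensitivity analysis.

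**The concern.** The design draws its credibility from allocation by admitting hospital, unrelated to who the patient is. Two provisions weaken that.

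First, in the mixed hospital early or delayed timing follows the procedure. A written rule that allocates by procedure is free of surgeon choice, but it is not free of confounding by procedure. If prosthesis and other procedures carry different transfusion risks, this hospital makes the procedure mix of the two cohorts unequal, and the crude risk difference carries that imbalance to the margin.

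Second, the unit of allocation is the hospital in sections 5.2.2 and 5.8.1 and in the Figure 2 legend, but the surgeon in section 5.2.3 once a change occurs. Where the two disagree, cohort membership is undefined in the primary per-protocol analysis and in the ITT analysis meant to check it. Recruitment is affected too, because section 5.7 closes each school at 187 adherent patients.

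**Working it through.** **The plan's own figure.** Section 5.7 gives rates of 15% (delayed) and 10% (early), a 5-point margin, one-sided alpha 0.05 and 90% power. The distance to the margin is 0.05 + 0.05 = 0.10, so

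n = (1.645 + 1.282)² × (0.15 × 0.85 + 0.10 × 0.90) / 0.10² = 186.3, rounded up to 187 per group.

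This reproduces the stated 187 and 374, and the point does not dispute them.

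**Part 1: size of the procedure imbalance.** The documents give neither the mixed hospital's volume, nor its prosthesis share, nor transfusion risk by procedure. Assumptions: equal volumes, so 374/7 = 53.4 patients from this hospital; prosthesis share a of 40–50% in every hospital; transfusion risk differing by d = 5, 10 or 15 points between prosthesis and other procedures; no timing effect on top.

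At a = 50%, the hospital sends 26.7 prosthesis patients to the delayed cohort and 26.7 others to the early cohort. The shift in the risk difference is 26.7 × d / 187:

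- d = 5: 0.7 points
- d = 10: 1.4 points
- d = 15: 2.1 points

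More generally, let the mixed hospital sit alongside nA purely early and nB purely delayed hospitals. The prosthesis share is nA·a/(nA + 1 − a) in the early cohort and (nB·a + a)/(nB + a) in the delayed cohort. The shift is d times the gap between them. Since 3 + 4 = 7, the mixed hospital is already counted in one school, and the text does not say which, so both layouts are shown.

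| Pure early / pure delayed | a | Prosthesis share, early | Prosthesis share, delayed | Shift at d = 5 / 10 / 15 (points) |
|---|---|---|---|---|
| 3 / 3 | 40% | 33.3% | 47.1% | 0.7 / 1.4 / 2.1 |
| 3 / 3 | 50% | 42.9% | 57.1% | 0.7 / 1.4 / 2.1 |
| 2 / 4 | 40% | 30.8% | 45.5% | 0.7 / 1.5 / 2.2 |
| 2 / 4 | 50% | 40.0% | 55.6% | 0.8 / 1.6 / 2.3 |

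If prosthesis patients are transfused more, early minus delayed moves down, towards non-inferiority. If the other procedures are transfused more, it moves up by the same amount.

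**What such a shift does to the test** (187 per group, shifts of 0.7, 1.4 and 2.1 points):

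- At the margin, with true rates of 20% early and 15% delayed, SE = √[(0.20 × 0.80 + 0.15 × 0.85)/187] = 3.92 points. A favourable shift raises the chance of wrongly concluding non-inferiority, Φ(−1.645 + shift/3.92), from 5% to about 7%, 10% and 14%.
- At the planned rates of 10% and 15%, SE = 3.41 points. An unfavourable shift lowers power, Φ((10 − shift)/3.41 − 1.645), from 90% to about 86%, 81% and 75%.

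**Part 2: the reallocation rule.** Take a patient in a School B hospital whose written policy is unchanged, operated on early by a surgeon who has adopted early surgery as standing practice.

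| Source | Rule | Cohort |
|---|---|---|
| 5.2.2 | Institutional protocol, not surgeon | School B |
| 5.2.3 | Surgeon-level protocol after a change | School A, adherent |
| 5.8.1, per-protocol | Adherence to the hospital's protocol | School B, timing off protocol, excluded |
| 5.8.1, ITT | Admitting hospital's timing policy | School B |
| Figure 2 legend, ITT | Initially assigned cohort by hospital protocol | School B |

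If all surgeons in a hospital change together, the hospital's policy has in effect changed and sections 5.2.3 and 5.8.1 can agree. The conflict is confined to a partial change.

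**The case against.** Much can be said for the plan. Six of the seven hospitals allocate by hospital unless practice changes. The mixed hospital is disclosed and its written policy is stated. Procedure is recorded, is listed for the logistic model, and matching is planned. Section 5.2.1 accepts surgeon preference as an allocation mechanism, so a surgeon-level fallback lies within the declared framework. The change is called unlikely, and neither section 5.8.1 nor the Figure 2 legend names it as a deviation. The inputs to the size estimate come from no document; at a 15% mean and an equal split, a 15-point gap means 7.5% against 22.5%.

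These points limit the finding and rule out several stronger readings that a reader might infer:

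- **That ITT is undefined at the mixed hospital.** Applying its written policy patient by patient gives each patient one value, and that is the natural reading of sections 5.2.2 and 5.8.1. Classing the hospital whole and excluding one procedure group as deviating is stated nowhere. Figure A1 and the body of Figure 2 are not available, so they cannot be used either way.
- **That allocation is not by hospital in general.** It is, in six centres, absent a change.
- **That the surgeon rule lets hand-picked early cases into School A and undoes the quasi-randomisation.** The trigger is a change of protocol, not a case-by-case choice. A single urgent early operation in School B remains a deviation under section 5.2.2.

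The objection does not remove two things. Neither the adjusted odds ratio nor the matched analysis supplies the risk difference tested against the margin. And the surgeon-level and hospital-level rules still give different cohorts for the same patient after a partial change.

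**Conclusion.** The point holds in two limited parts.

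In one hospital of seven, allocation depends on procedure, so the independence claimed in section 5.2.3 fails there, and the unadjusted primary risk difference is open to confounding by procedure. Under the stated assumptions the shift is about 0.7 to 2.1 points of the 5-point margin, or up to 2.3 if only two hospitals are purely early. The direction is unknown: the documents do not show that the bias favours early surgery, or that it is large. The firm finding is the structural imbalance; its size is illustrative.

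Section 5.2.3 also conflicts with section 5.2.2, section 5.8.1 and the Figure 2 legend when only some surgeons in a hospital change. This is contingent on an event the plan thinks unlikely, and no size can be put on it. It is still a contradiction between stated rules, not a detail left to an analysis plan. Both parts should be corrected before outcomes are analysed; neither invalidates the design.

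**What to change.** 1. State that the mixed hospital's patients are classified by its written procedure-specific policy in both the per-protocol and ITT analyses, and say how the hospital is counted among the three and four.
2. Standardise or stratify the primary risk difference, with its one-sided 95% limit, by prosthesis versus other procedures. Procedure is already recorded.
3. Pre-specify a sensitivity analysis that omits this hospital.
4. Limit the independence claim in section 5.2.3 to the hospitals where it applies.
5. Reconcile sections 5.2.2, 5.2.3 and 5.8.1 and the Figure 2 legend into one prospective, dated reallocation rule used identically in both populations and in the count towards 187. One workable form keeps patients in their original school for ITT unless the hospital's own policy changes. Other rules are defensible, provided there is only one.

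The cost is protocol wording, one stratified or standardised estimate and one sensitivity analysis, with no change to care. A strict rule may also yield fewer per-protocol patients after a surgeon-level change, because patients treated consistently under a new personal practice would not count.

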#### 5.2.3. Policy Changes

Initially, allocation to these groups occurs naturally based on the hospital where the patient is admitted, rather than by investigator intervention, ensuring that treatment allocation is independent of individual patient characteristics. However, in the unlikely event that during the study (orthopedic) trauma surgeons within School “B” change their protocol and start performing surgery within 24 h after last DOAC intake, these patients will be included in School “A”. Conversely, if surgeons within School “A” change their protocol to delay surgery at least 24 h after last DOAC intake, patients from that point onward will be included in School “B”. In both cases, allocation will then be based on surgeon-level protocol rather than hospital-level standard practice. Despite this, the study remains a natural experiment, as patients continue to be quasi-randomly allocated to comparable level 2 trauma centers with uniform hospital resources and patient populations.

### 5.3. Eligibility Criteria

Patients are eligible for inclusion if they present with an isolated hip fracture classified as AO/OTA 31A or 31B, requiring surgical intervention, are actively using DOACs and have taken their DOAC within 24 h before ED presentation (Figure 1) [46]. Exclusion criteria include pathological or periprosthetic fractures, fractures sustained more than 24 h before ED presentation, and transfers to another hospital. Patients with hematologic disorders or disruptions (i.e., thalassemia, sickle cell disease, aplastic anemia, myelodysplastic syndromes, or leukemia) will also be excluded, as will those using a non-approved DOAC (i.e., betrixaban) by the European Medicines Agency. Patients presenting to the ED more than 24 h after fracture occurrence are excluded, as delayed presentation introduces uncertainty regarding active DOAC exposure in the early surgery cohort. In such cases, anticoagulant activity may have substantially declined irrespective of institutional surgical timing protocols. Although this exclusion may limit generalizability and introduce selection bias, it was considered necessary to preserve internal validity and ensure meaningful comparability between early and delayed surgery cohorts.

### 5.4. Baseline Characteristics

The following baseline characteristics will be collected: age, sex, preoperative estimated glomerular filtration rate (eGFR in mL/min/1.73 m^2^), preoperative hemoglobin (Hb in mmol/L), preoperative hematocrit (Ht in L/L), type of DOAC (apixaban, edoxaban, rivaroxaban, or dabigatran), DOAC dosage, DOAC indication, hours since last DOAC intake, concurrent use of antiplatelet medication (yes/no), and the specific type of concurrent antiplatelet or anticoagulant medication used. Frailty indicators include a prior diagnosis of dementia (by a geriatrician or general practitioner), Body Mass Index (BMI in kg/m^2^), Short Nutritional Assessment Questionnaire (SNAQ) score, Clinical Frailty Scale (CFS), Charlson Comorbidity Index (CCI), American Society of Anesthesiologists (ASA) score, number of daily medications, pre-fracture living situation (independently at home, with assistance in Activities of Daily Living (ADL), or in institutional care facility), household composition (living alone, with a partner, or with family), pre-fracture mobility (based on the Fracture Mobility Score), and Katz-6 ADL score [47,48,49,50,51,52]. Fracture characteristics include the type of fracture (based on AO/OTA classification) and the surgical procedure performed (hemiarthroplasty, total hip arthroplasty, intramedullary nail, sliding hip screw, or cannulated hip screw) [46]. Lastly, the type of anesthesia (general or spinal), any preoperative use of tranexamic acid, fibrinogen, or platelet concentrates, and DOAC reversal agents (idarucizumab or andexanet alfa) will be registered. In addition, patients whose surgery was delayed for reasons unrelated to DOAC use will be documented, along with the specific reason for the delay. Measurement of DOAC plasma levels is not part of routine care in the participating centers and is therefore not included.

### 5.5. Outcomes

#### 5.5.1. Primary Outcome

The primary outcome of this study is postoperative blood transfusion, defined as the administration of one or more units of packed red blood cells (PRBCs) postoperatively during admission. This outcome serves as a robust, objective, and clinically relevant marker of perioperative blood loss. Transfusion is a widely used endpoint in studies evaluating surgical bleeding, as it reflects a clinical decision based on pre-, intra- and postoperative hemodynamics, Hb thresholds, and clinical symptoms. Unlike subjective measures such as hematoma grading or intraoperative blood loss estimates, transfusion requirement provides a clear, binary outcome with direct clinical implications for patient recovery and safety. Inter-hospital variation in transfusion practices is likely to be minimal, because all participating hospitals adhere to the 4–5–6 rule or the Dutch national transfusion guideline (2020) [53]. Although minor differences in transfusion policies may exist between participating centers, these are expected to be evenly distributed across study cohorts and these will not be altered to preserve the natural experiment design. Moreover, variability at the level of individual providers is inherent to routine clinical care and is expected to occur similarly across all participating centers, making systematic differences between groups unlikely. In conclusion, any inter-hospital variation in transfusion thresholds is expected to be non-differential between the early and delayed surgery cohorts, as transfusion decisions are not systematically related to surgical timing. Such non-differential variability would be expected to bias effect estimates toward the null, thereby reducing the risk of falsely concluding non-inferiority.

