Despite its clinical relevance, no consensus exists in the literature on the optimal surgical timing after DOAC discontinuation in hip fracture patients [12,27,29]. The uncertainty about this dilemma is reflected in clinical practice: 74% of surgeons consider current guidelines for hip fracture patients on DOACs inadequate, contributing to substantial clinical practice variation across hospitals [12,13,30,31]. Consequently, some hospitals postpone surgery for at least 48 h to mitigate bleeding risk, and some determine the timing of surgery based on renal function [12,13,30]. Retrospective studies suggest that early surgery may be safe; however, only one single-center study has directly compared the outcome of surgery performed within 24 h to after 24 h or more [27,32,33,34]. Nonetheless, expert consensus in several Dutch hospitals now permits immediate surgery for hip fracture patients on DOACs, as concerns also extend to preoperative blood loss from ongoing bleeding in unstabilized fractures [35,36,37].

This study will evaluate whether surgery within 24 h after last DOAC intake is as safe as surgery after 24 h or more in hip fracture patients on DOACs with respect to bleeding risk. Postoperative blood transfusion was chosen as the primary outcome because it represents a clinically relevant and objectively recorded outcome in routine practice. The hypothesis is that early surgery within 24 h results in a non-inferior postoperative blood transfusion risk compared to delayed surgery 24 h or more after last DOAC intake in hip fracture patients on DOACs. This protocol article outlines the design and methodological rationale of a natural experiment.

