### 5.7. Sample Size and Rationale for Non-Inferiority

The research question of this study is framed as a non-inferiority comparison, and the sample size has therefore been calculated to test non-inferiority. This study used the most recent institutional data, as these best reflect the clinical context and patient population of this study. These institutional data showed a transfusion rate of approximately 15% in the delayed surgery group and 10% in the early surgery group, which is considered appropriate for powering a non-inferiority analysis in this natural experiment. In consultation with clinical experts, a non-inferiority margin (ΔNI) of 5% is deemed clinically acceptable to conclude that early surgery does not result in a clinically relevant increase in transfusion requirement. Non-inferiority will be demonstrated if the upper bound of the one-sided 95% confidence interval for the absolute risk difference between groups remains below 5%. Based on these assumptions, an expected event rate of 15% in the control group and 10% in the intervention group, with a one-sided alpha of 0.05 (Zα = 1.645) and a power of 90% (Zβ = 1.282), the required total sample size is 374 patients, with 187 per group.

As the sample size is based on the per-protocol population, patient inclusion will continue until 187 patients per treatment group have been included who adhered to the protocol of their respective school of treatment (Figure 2). Inclusion in a given school will stop once the required number of per-protocol patients (*n* = 187) is reached in that group. The other school will continue including patients until it also reaches the target of 187 per-protocol patients. As a result, the intention-to-treat population is expected to exceed 374 patients. Since the primary outcome is assessed during hospitalization, no loss to follow-up is anticipated. This approach provides sufficient power to robustly assess non-inferiority within the specified parameters.

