### 5.8. Statistical Analysis

#### 5.8.1. Primary Outcome

The primary outcome is postoperative blood transfusion in hip fracture patients on DOACs. To assess non-inferiority of early surgery within 24 h compared to delayed surgery 24 h or more after last DOAC intake, the risk difference in transfusion requirement between both groups will be calculated with a corresponding one-sided 95% CI. Non-inferiority will be concluded if the upper bound of the one-sided 95% CI does not exceed the predefined non-inferiority margin of 5%.

In addition, a multivariable logistic regression analysis will be performed to estimate the adjusted odds ratio (aOR) and associated 95% CI for transfusion requirement, adjusting for potential confounders. Based on literature and expert-opinion, the following variables will be considered for inclusion in the regression model: sex, preoperative Hb, Clinical Frailty Scale, and type of surgical procedure [59,60,61,62]. Given a total sample size of 374 and an expected event rate of 15%, approximately 56 events are anticipated, allowing for inclusion of up to five independent variables, in accordance with standard rules to prevent model overfitting.

The primary analysis will follow a per-protocol approach, in which patients will be analyzed based on adherence to the surgical timing protocol of their respective hospital (i.e., within 24 h for School “A” centers and after 24 h or more for School “B” centers). Patients whose surgical timing deviates from this hospital protocol will be identified and excluded from the per-protocol analysis (Figure 2). In addition, an intention-to-treat (ITT) analysis will be conducted, in which patients will be analyzed according to the timing policy of their admitting hospital, regardless of actual timing. This ITT analysis will serve to assess the robustness of the findings, while preserving the effect of quasi-randomization and limiting the risk of confounding by indication. As a sensitivity analysis, propensity score matching will be applied to further assess robustness of the primary findings. This analysis will allow comparison of results obtained using propensity score matching with those derived from the natural experiment design and provide additional insight into the methodological value of the natural experiment approach.

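### Bias toward no difference is described as guarding against a false non-inferiority conclusion; under the plan's own decision rule it makes one more likely

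*Protocol article*

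**What the plan says.** Section 5.5.1 defines the primary outcome as at least one unit of packed red cells given after surgery during the admission. It expects little variation between hospitals because all follow one of two named transfusion rules. It then allows for some variation ("Although minor differences in transfusion policies may exist between participating centers"), states that local policies will be left as they are, and concludes that "any inter-hospital variation in transfusion thresholds is expected to be non-differential between the early and delayed surgery cohorts". The argument closes with: "Such non-differential variability would be expected to bias effect estimates toward the null, thereby reducing the risk of falsely concluding non-inferiority".

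The hypothesis in section 2 is that "early surgery within 24 h results in a non-inferior postoperative blood transfusion risk compared to delayed surgery 24 h or more". Section 5.8.1 gives the decision rule: "Non-inferiority will be concluded if the upper bound of the one-sided 95% CI does not exceed the predefined non-inferiority margin of 5" percent. Sections 4.1 and 5.7 state the same rule as the bound remaining below 5%. Section 5.7 plans for "an expected event rate of 15% in the control group and 10% in the intervention group", with one-sided alpha 0.05, 90% power and 187 patients per group.

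**The concern.** In a superiority test the hypothesis to be rejected is no difference, so bias toward no difference makes a false positive less likely. In this study the hypothesis to be rejected is that early surgery raises transfusion risk by 5 points or more. No difference lies inside the region where non-inferiority is declared, and bias toward it favours the declaration. The sentence in section 5.5.1 carries the superiority argument into a design where it runs the other way.

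The sentence is the last step in the reasoning by which the plan sets aside transfusion practice as a threat to its primary outcome. If the study reports non-inferiority, a reader relying on it would take this source of error as conservative and trust the result more than is warranted. Section 3 says that such a result would support a major change in practice.

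**Working it through.** **Inputs.** From section 5.7: 15% transfused in the delayed group, 10% in the early group, margin 5 points, one-sided alpha 0.05 (z = 1.645), power 90% (z = 1.282), 187 per group. From section 5.8.1: the upper-bound rule. Assumed, because the documents give no figure: the fraction a by which the risk difference is attenuated.

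**1. The plan's sample size.** n per group = (0.15 × 0.85 + 0.10 × 0.90) × (1.645 + 1.282)² / (0.05 + 0.05)² = 186.3, rounded up to 187, or 374 in total. This reproduces the stated figure. Power at the design point is 90.1%. The sample size is not in dispute.

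**2. When the conclusion can be false.** Let RD be the risk in the early group minus the risk in the delayed group. A non-inferiority conclusion is false only if the true RD is at least +5 points. Attenuation replaces RD by RD × (1 − a), which lies closer to zero and so on the favourable side of where it was.

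**3. Size at the margin.** P(conclude non-inferiority) = Φ((0.05 − RD_obs)/SE − 1.645), where SE is the unpooled standard error with 187 per group. The delayed risk is held at 15% and the true early risk is 20%.

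| Assumed a | RD_obs | SE | P(false non-inferiority) |
|---|---|---|---|
| 0 | 5.0 points | 0.0392 | 5.0% |
| 10% | 4.5 points | 0.0390 | 6.5% |
| 20% | 4.0 points | 0.0388 | 8.3% |
| 30% | 3.5 points | 0.0386 | 10.5% |
| 50% | 2.5 points | 0.0381 | 16.1% |

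For example, at a = 30%: SE = √((0.15 × 0.85 + 0.185 × 0.815)/187) = 0.0386, and (0.05 − 0.035)/0.0386 − 1.645 = −1.256, so Φ = 10.5%.

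**4. A second way of producing attenuation.** If transfusion is treated as an imperfect marker of bleeding with the same sensitivity and specificity in both groups, RD_obs = (Se + Sp − 1) × RD. From true risks of 20% v 15%, the false conclusion rate is 6.5% (Se/Sp 0.90/1.00), 8.6% (0.80/1.00), 7.2% (0.90/0.95), 7.8% (0.90/0.90) and 9.8% (0.80/0.90). These pairs are also assumptions. Exact binomial enumeration gives similar values, for example 6.9% for the first pair and 7.4% for the third.

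**5. A larger true harm.** At 23% v 15% (RD +8 points) the rate is 0.9% without attenuation, 1.4% at a = 10% and 8.3% at a = 50%.

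**6. The design alternative.** At 10% v 15% (RD −5 points), attenuation of the difference lowers the chance of concluding non-inferiority from 90.1% to 86.8% (a = 10%), 82.8% (20%) and 67.8% (50%). Here the conclusion would be true, so what is lost is power.

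**The case against.** The strongest defence is that the plan expects early surgery to do better, and in that case attenuation does make a non-inferiority conclusion less likely. That is so, but the conclusion would then be correct. The sentence speaks of falsely concluding non-inferiority, which cannot happen in that case.

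A second defence is that the outcome is transfusion itself. A different threshold does not misrecord whether blood was given, and it need not shrink the absolute risk difference by any fixed fraction. This stands as a limit on the figures: the attenuation is the plan's own premise, taken at its word, and its amount is unknown. It does not rescue the sentence. If there is no attenuation, there is no protective effect to claim either.

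Third, the sentence sets no margin, estimator, population or decision rule. That also stands: the correction changes how a result is interpreted, not how it is computed.

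Two stronger readings are tempting and not supported. A reader might infer that nothing is planned that bears on transfusion practice. In fact section 5.8.1 plans an intraclass correlation by centre with a multilevel model if clustering is found, an intention-to-treat analysis and propensity score matching, and sections 5.5.2 and 5.8.2 include haemoglobin-based outcomes. What can be said is that none of these is directed at attenuation of the primary risk difference. A reader might also infer that transfusion rules differ systematically between the schools, since each of seven hospitals follows one of two rules. The documents do not say how the rules are distributed or whether their thresholds differ in practice. Differential practice would be a separate threat that could bias in either direction, and the figures above do not model it.

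**Conclusion.** The statement in section 5.5.1 is wrong as written, and nothing elsewhere in the article corrects it. Under the rule in sections 4.1, 5.7 and 5.8.1, bias toward no difference raises the risk of a false non-inferiority conclusion. With a true excess exactly at the margin and 187 per group, the rate goes from 5% to about 6.5% at 10% attenuation and about 16% at 50%. These values rest on assumed attenuation and on a true effect 10 points away from the one the plan expects (+5 rather than −5), so they show direction and scale and do not forecast this study's error rate. The direction does not depend on the amount assumed.

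**What to change.** 1. Replace the sentence in section 5.5.1 with one saying that non-differential variation which biases toward no difference raises the risk of falsely concluding non-inferiority, and that this is an anti-conservative threat to be weighed when interpreting a positive result.
2. Record which transfusion rule each centre follows and tabulate it by school.
3. Report between-group differences in the bleeding index and in the proportion with an Hb decrease of more than 2 mmol/L beside the primary result, as supportive evidence. Both are already collected. State that the interval from emergency department Hb to lowest postoperative Hb includes preoperative loss, over a longer wait in delayed patients, and that transfusion can mask an Hb fall (the bleeding index adds transfused units back).

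These supportive outcomes should not become a condition for concluding non-inferiority. That would rewrite the primary decision rule and cost power: if the groups truly did not differ on the Hb outcome, its estimate would point the wrong way about half the time.

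The cost is one centre-level variable, a little extra analysis of existing data and a less favourable statement about bias. Sample size, margin and patient care are unchanged.
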